#### Fire needle control group

In this group, the operators will directly penetrate the skin lesion without heating the needle. All other procedures will remain the same as those described for the intervention group.

After treatment, all patients will receive an explanation that redness, warmth, mild pain, and/or itching at the acupuncture sites are normal side effects that will resolve on their own. Moreover, they will be instructed to maintain cleanliness at the acupuncture sites, avoid scratching with their hands, refrain from using oils or creams, and refrain from exposing the punctured sites to water on the day of treatment.

### Outcomes

#### Primary outcomes

The Psoriasis Area and Severity Index (PASI) is the gold standard assessment tool used to quantify the severity of psoriasis based on erythema, infiltration, scaling, and the extent of lesions [16]. As such, a decrease in the PASI score has been designated as the primary outcome of this study. This score will be evaluated at screening, at baseline, during the 4-week treatment period, and during the 4-week follow-up period. The researchers will use the PASI to assess the severity and area of lesions and simultaneously obtain photographs of typical skin lesions.

#### Secondary outcomes

Secondary outcomes will include the BSA and Physician Global Assessment (PGA) score to describe the severity of psoriasis. The BSA will also be used to estimate the body area of psoriasis lesions, and PGA scores will be used to compare the baseline conditions of patients with psoriasis [17]. As itching is a common symptom of psoriasis, a visual analog scale (VAS) will be used to evaluate the degree of itching. Apart from these, we will also use two tools to assess the quality of life of patients with psoriasis: The Dermatology Life Quality Index (DLQI) [18] and the patient-reported quality of life (PRQoL). TCM symptoms will be assessed using TCM symptom scores, which are formulated according to TCM diagnostic criteria. When scoring, patients only need to answer “yes” or “no”; “yes” counts as 1 point, “no” counts as 0 points, and the points are combined to calculate the total score (Table 1). The recurrence rate will also be calculated to evaluate the efficacy of fire needle therapy.

**Table 1 Tab1:** TCM symptom scores for blood stasis syndrome of plaque psoriasis

Symptoms	Scores	
The prolonged presence of dark red skin lesions	0, No	1, Yes
The prolonged presence of hypertrophic, infiltrating skin lesions	0, No	1, Yes
Scaly dry skin, a soot-black facial complexion, cyanosis of the lips and nails	0, No	1, Yes
Dark menstrual blood or blood clots in female patients	0, No	1, Yes
A dark purple tongue with ecchymosis and/or petechiae	0, No	1, Yes
An unsmooth pulse and a thready/moderate pulse	0, No	1, Yes
Total scores		

The BSA, PGA, and VAS scores will be evaluated along with the PASI score at baseline and during the treatment and follow-up periods. The PRQoL, DLQI, and TCM symptom scores will be assessed at baseline and during the 4-week treatment period, while recurrence will be assessed during the follow-up period. For this study, recurrence is defined as a follow-up PASI score exceeding the score at the time of enrollment, the appearance of new pustules during the follow-up period, or the development of erythroderma during the follow-up period. Once recurrence is confirmed, the participant will be given the option of terminating the follow-up and initiating other treatments.

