### Diagnostic criteria

In Western medicine, the diagnostic criteria for plaque psoriasis have been formulated in accordance with *Guideline for the diagnosis and treatment of psoriasis in China (2018 simplified edition)* [13], whereas those for BSS of plaque psoriasis have been drafted according to the *Evidence-based clinical practice guide for psoriasis vulgaris* by the Dermatology Branch of China Association of Chinese Medicine [14].

Accordingly, participants will be diagnosed with plaque psoriasis based on the following criteria [13]: First, the skin lesions appear as dark red plaques or invasive erythema with clear boundaries showing white or silvery-white scales. Second, features such as the “wax drop phenomenon,” “film phenomenon,” “point bleeding phenomenon” (Auspitz sign), and “bundle hair” can be found during physical examination. Third, the scalp, back, and extremities are the most susceptible areas for skin lesions. Fourth, itching may or may not be present. Fifth, the Koebner phenomenon can be observed in the advanced stage. Finally, the skin lesions are prone to relapse, with the majority alleviated in summer and aggravated in winter.

The main sign of BSS of plaque psoriasis is the prolonged presence of dark red, hypertrophic, infiltrating skin lesions. Minor signs include scaly dry skin, a soot-black facial complexion, cyanosis of the lips and nails, dark menstrual blood or blood clots in female patients, a dark purple tongue with ecchymosis and/or petechiae, an unsmooth pulse, and a thready/moderate pulse. The presence of BSS will be confirmed when patients show the main sign along with more than one minor sign [14, 15].

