### Inclusion and exclusion criteria

Participants will be recruited from five hospitals in China: Shaanxi Hospital of Traditional Chinese Medicine, Yueyang Hospital of Integrated Traditional Chinese and Western Medicine, First Affiliated Hospital of Heilongjiang University of Traditional Chinese Medicine, Affiliated Hospital of Jiangxi University of Traditional Chinese Medicine, and Traditional Chinese Medicine Hospital of Shijiazhuang. Each research center has one or two clinical research observers (CRO) who will explain this trial to participants before they voluntarily sign an informed consent form at the beginning of the study. On the consent form, participants will be asked if they agree to the use of their data, should they choose to withdraw from the trial. Participants will also be asked to grant permission for the research team to share relevant data with the universities taking part in the research or regulatory authorities, where relevant. This trial does not involve the collection of biological specimens for storage.

The general inclusion criteria for the study are as follows: (1) compliance with the abovementioned diagnostic criteria for plaque psoriasis and BSS of plaque psoriasis; (2) skin lesions involving ≤ 10% of the body surface area (BSA), with primary involvement of the trunk and/or limbs, palms/soles, and/or face/scalp (vulva not included); (3) aged 18 to 65 years (inclusive of 18 and 65 years); and (4) provision of written informed consent for participation in the study.

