### Statistical analysis

A statistician will formulate a plan for statistical analysis in consultation with the PI. All analyses will be conducted using SAS statistical software, and the data network platform will be designed by the data management center of Nanjing Ningqi Medical Technology Co., Ltd., which will be entrusted with the third-party statistical analyses. The measurers will be blinded to the results. The overall principles will be as follows: An intention-to-treat (ITT) and per-protocol analysis will be used for statistical analysis. Quantitative variables (such as PASI, BSA, PGA, DLQI, PRQoL, VAS, and TCM syndrome scores) will be expressed as mean and standard deviation values or as median values with lower (Q1) and upper (Q3) quartiles. If the quantitative variables conform to normal distribution, a *t* test will be used (The homogeneity test will be performed for the two groups, with 0.05 as the significance level. The Satterthwaite method will be used to correct the *t* test when the variance is not uniform). If quantitative variables conform to skewed distribution, a nonparametric test will be used. Qualitative variables (such as cure rate, recurrence rate) will be expressed as numbers and percentages or composition ratios. Statistical inference will be performed using chi-square tests, Fisher’s exact tests, and Wilcoxon rank sum tests, among others. Potential confounding factors affecting the main outcome indicators will be adjusted by logistic regression. In this study, a *p* value of less than 0.05 is considered as statistically significant.

To account for missing data, we considered participants who may not complete the follow-up when calculating the sample size. The reasons, main characteristics, and data of a patient’s failure to follow-up will be recorded. Other types of randomly missing data will be considered unsuccessful according to the principle of ITT analysis.

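### Itch VAS gets an unadjusted t or rank test although patients may enter without itch; baseline VAS as covariate would recover power at no cost

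*Protocol article*

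**What the plan says.** All places are in the protocol article.

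- Diagnostic criteria: "Fourth, itching may or may not be present".
- Inclusion and exclusion criteria: the four inclusion criteria cover diagnosis, lesion extent and site ("skin lesions involving ≤ 10% of the body surface area (BSA), with primary involvement of the trunk and/or limbs, palms/soles, and/or face/scalp"), age and consent. None sets a minimum itch score.
- Secondary outcomes: "As itching is a common symptom of psoriasis, a visual analog scale (VAS) will be used to evaluate the degree of itching". On timing: "The BSA, PGA, and VAS scores will be evaluated along with the PASI score at baseline and during the treatment and follow-up periods". Table 2 confirms a baseline VAS.
- Statistical analysis: "An intention-to-treat (ITT) and per-protocol analysis will be used for statistical analysis". VAS is named in the list of scores: "Quantitative variables (such as PASI, BSA, PGA, DLQI, PRQoL, VAS, and TCM syndrome scores) will be expressed as mean and standard deviation values" or as medians with quartiles. Normally distributed variables get a t test. For the rest, "If quantitative variables conform to skewed distribution, a nonparametric test will be used". The only adjustment named is logistic regression for the main outcome indicators, which does not reach VAS.
- Sample size: based on the cure rate alone. No effect, SD or power is given for VAS.

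**The concern.** Patients with and without itch enter together and may differ by several VAS points before any treatment is given. An unadjusted test carries that spread as noise. If Week 4 values are compared, all of the baseline spread is in the error term. If changes are compared, much of it cancels, but patients at zero who stay at zero are mixed with patients who improve, and that mixture adds variance. A block of zeros also makes skew likely, which would send VAS to the nonparametric branch.

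Two things are at stake. The itch comparison is less sensitive than the collected data allow. And the all-patient mean difference is smaller than the relief that an itching patient can expect, which a reader of the trial report may want to know.

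**Working it through.** **The plan's own figure.** The only calculation is for the cure rate: [0.768×0.232 + 0.353×0.647] / (0.768 − 0.353)² × (1.960 + 1.282)² = 0.4066/0.1722 × 10.51 = 24.8, so 25 per group as stated. This is raised to 38, then to 47 for 20% dropout (38/0.8 = 47.5). It reproduces to within rounding and says nothing about VAS.

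**Assumed inputs (none is in the article).** Patients with itch: baseline mean 5.5, SD 2; residual SD of change s = 2.2; control improvement 1.5; extra treatment effect δ = 1.5; scores cannot go below 0. Patients without itch start and stay at 0; their share is f = 10 to 40%. Mean change in itching patients, averaged over arms and before the floor: m = 1.5 + 1.5/2 = 2.25.

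**Step 1, size of the mean difference.** With no itch-free patients the floor reduces the effect from 1.5 to about 1.27. With a share f it becomes (1 − f) × 1.27 = 1.14, 1.02, 0.89 and 0.76 at f = 10, 20, 30 and 40%.

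**Step 2, unadjusted change scores.** Over all patients the difference is (1 − f)δ and the within-arm variance is (1 − f)s² + f(1 − f)m². The test statistic is then proportional to √[n(1 − f)] × δ/√(s² + f·m²). In itching patients only it is proportional to √[n(1 − f)] × δ/s. The ratio is s/√(s² + f·m²), with s² = 4.84 and m² = 5.06:

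- f = 10%: 2.2/√5.35 = 0.95
- f = 20%: 2.2/√5.85 = 0.91
- f = 30%: 2.2/√6.36 = 0.87
- f = 40%: 2.2/√6.87 = 0.84

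**Step 3, unadjusted Week 4 values.** The baseline spread now stays in. Variance in itching patients is 2² + 2.2² = 8.84, and their Week 4 mean is about 5.5 − 2.25 = 3.25 (floor ignored). The ratio is 2.2/√(8.84 + f × 3.25²). At f = 20% this is 2.2/√10.95 = 0.66.

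**Step 4, power by simulation, 47 per group, two-sided 0.05, 2,000 trials per setting.**

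| Share without itch | 10% | 20% | 30% | 40% |
|---|---|---|---|---|
| Week 4 values, t test, all patients | 54% | 43% | 35% | 28% |
| Change, rank test, all patients | 76% | 63% | 52% | 44% |
| Change, t test, all patients | 80% | 71% | 61% | 50% |
| Change, t test, itching patients only | 84% | 79% | 72% | 67% |
| ANCOVA with baseline VAS, all patients | 83% | 77% | 71% | 65% |
| ANCOVA with baseline VAS, itching patients only | 84% | 79% | 73% | 66% |

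Gain of all-patient ANCOVA over the t test of change: 83 − 80 = 3, 77 − 71 = 6, 71 − 61 = 10, 65 − 50 = 15 points. Each power figure has a simulation error of up to √(0.25/2000) = 1.1 points, so about 2 to 17 points is a fair summary. The two ANCOVA rows differ by at most 2 points.

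**Step 5, the planned 38 evaluable per group, 20% without itch.** Simulated power: 35% for Week 4 values, 60% for change by t test, 55% by rank test, 68% for ANCOVA in all patients, 70% for ANCOVA in itching patients only. Steps 2 and 3 agree with this. A power of 68% means an expected z of 1.96 + 0.47 = 2.43. Then 2.43 × 0.91 = 2.21 gives 60%, and 2.43 × 0.66 = 1.60 gives 36%.

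**Sensitivity.** If the control arm improves by only 0.5 point, m is smaller and the gap between all patients and itching patients, for change scores, shrinks to about 1, 2, 4 and 7 points.

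**The case against.** **No stated figure is wrong.** The article offers overall principles and says that a statistician will write the analysis plan. Analysis sets and covariates for one secondary score are often left to that plan, and an intention-to-treat comparison of all patients is a normal default. This stands as a limit on how strongly to put the point. It does not remove it, because the article does name VAS and does name its tests.

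**The share without itch may be small.** The article itself calls itching common. At 10% the gain over a test of change is about 3 points. This also stands.

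**A reader might infer that patients without itch add nothing and should leave the main itch analysis.** The documents do not support that. Under Interventions (Fire needle control group), patients in both arms are told that itching at the puncture sites is an expected side effect. A patient who starts at 0 can therefore worsen, possibly at different rates with heated and unheated needles. Leaving these patients out of the main comparison would drop those who can only worsen and tilt the result towards benefit. The table also shows that exclusion brings at most 2 points beyond baseline adjustment. A cut at VAS above 0 is somewhat arbitrary too, since a patient at 0.5 faces almost the same floor.

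**A reader might also infer that the all-patient result is biased, or that the trial breaks a power promise for itch.** Neither follows. The all-patient mean is a valid average over those enrolled; it is diluted, not biased. No power is claimed for VAS.

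**Conclusion.** The point holds as a free improvement, not as an error. The article names an unadjusted test for a score whose baseline it allows to run from none to severe, and it collects the baseline value that would remove most of the resulting noise.

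The direction is firm whenever patients with and without itch are both enrolled and the itching patients change on average. The size is not. It depends on the itch-free share, the VAS spread, the treatment effect and the control-arm improvement, none of which the article gives. Under the assumed inputs the gain is about 2 to 17 points against a test of change. At 38 per group and 20% without itch it is 68 − 35 = 33 points against a test of Week 4 values. The near-equality of all-patient and itch-only ANCOVA rests on itch-free patients mostly staying at 0.

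Adjustment does not restore everything. Power still falls as the itch-free share rises, because fewer patients carry information on relief, and the all-patient mean stays diluted by the factor (1 − f). The supportive analysis in itching patients addresses the second of these. The primary outcome is not affected.

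**What to change.** Take VAS out of the general t-or-nonparametric sentence and state its own analysis:

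1. Main itch comparison: all randomised patients, linear model for VAS with treatment arm and baseline VAS as covariate. Heteroscedasticity-robust standard errors are sensible, because patients without itch will vary less.
2. Supportive, prespecified: the same model in patients with baseline VAS above 0. The set is fixed before treatment, so the randomised comparison is kept, and it gives the relief that an itching patient can expect.
3. Report, by arm, the number and percentage of patients with baseline VAS 0 and the rate of new itch among them.

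The cost is a few lines of analysis text, to be settled before unblinding so that the supportive subset is not read as post hoc. Baseline VAS is already in Table 2, so no visit, measurement or patient is added. The supportive result uses fewer patients and applies only to those who itch at entry.

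### The TCM symptom total mixes a 0–6 and a 0–5 scale because one item can be scored only by menstruating women, and the plan states no adjustment for this when it compares the arms

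*Protocol article*

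**What the plan says.** Protocol article, Secondary outcomes and Table 1: the TCM symptom score has six items, each answered no (0) or yes (1), and "the points are combined to calculate the total score". One of the six is "Dark menstrual blood or blood clots in female patients". Table 1 shows no third response for patients to whom an item cannot apply, and no rescaling of the total.

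The item comes from the Diagnostic criteria section, which lists "dark menstrual blood or blood clots in female patients" among the minor signs of blood stasis syndrome (BSS).

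Inclusion and exclusion criteria: ages 18 to 65 with no restriction by sex, so men and postmenopausal women can enter.

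Timing: "The PRQoL, DLQI, and TCM symptom scores will be assessed at baseline and during the 4-week treatment period". Table 2 shows weeks 1, 2, 3 and 4. No recall period is given for any item.

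The Statistical analysis section puts the score among the continuous measures: "Quantitative variables (such as PASI, BSA, PGA, DLQI, PRQoL, VAS, and TCM syndrome scores) will be expressed as mean and standard deviation values". Medians with quartiles are the alternative summary, and the comparison is by a t test or a nonparametric test. I take the TCM syndrome score named there to be the Table 1 total. Adjustment for confounders is stated only for the main outcome indicators, by logistic regression. The section does not say whether the TCM score is compared as a post-treatment total or as change from baseline.

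**The concern.** A sex-specific sign does no harm in a diagnostic list, where the main sign plus more than one of several minor signs is enough. In an additive outcome score it does matter. Two patients with the same state on the other five items can differ by a point because only one of them can score the sixth. They also differ in how far they can improve.

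At stake is the precision and readability of one secondary outcome. Part of the spread in the totals reflects who is able to score the item and has nothing to do with treatment. If a woman's answer also varies between visits for reasons unrelated to treatment, that variation enters the change score.

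**Working it through.** **Plan's own figures.** The article gives no mean, SD or power for the TCM score, so there is no figure to reproduce for it. The group sizes come from the Sample size section: 38 per group before dropout and 47 per group after it (38/0.8 = 47.5; the plan states 47).

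**Attainable range (from Table 1).** Menstruating women: 6 items, 0–6. Everyone else: 5 items, 0–5. The item is 1/6 = 17% of the range for the first group and cannot be scored by the second.

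**Assumed inputs.** f = share of patients who menstruate, 0.2 to 0.5. q = share of those answering yes, 0.3 to 0.8. Variance of the other five items together, 0.5 to 1.25. None of these is in the article.

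**Chance imbalance, post-treatment totals, 47 per arm.**
- SE of the between-arm difference in menstruating share = √(2f(1−f)/47). At f = 0.5: √(2 × 0.25/47) = 0.103. At f = 0.2: √(2 × 0.16/47) = 0.083.
- Shift in the mean difference at 1.96 SE = 1.96 × SE × q. At f = 0.5, q = 0.5: 1.96 × 0.103 × 0.5 = 0.10 point. Over f 0.2–0.5 and q 0.5–0.8 the shift is about 0.08 to 0.16 point.

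**Share of variance due only to who can score the item.**
- Item variance = fq(1−fq), of which f(1−f)q² is eligibility alone.
- Low end (f = 0.2, q = 0.3, other variance 1.25): 0.0144/(1.25 + 0.0564) = 1.1%.
- High end (f = 0.5, q = 0.8, other variance 0.5): 0.16/(0.5 + 0.24) = 21.6%.

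**Bias.** With no treatment effect, simulated t tests on the six-item total (47 per arm) rejected in 4.4% to 5.3% of trials. The nominal level holds.

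**Power, post-treatment totals, 47 per arm (simulated).** If the item does not respond to treatment, power falls from about 0.81 to 0.73–0.79. If it responds like the others, power is 0.79–0.83 against 0.80–0.81 for the five items.

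**Power, change from baseline, 38 per arm (simulated).** Assumed: the other five items each present in 70% at baseline, resolving in 45% against 25%. Without the menstrual item, power is 0.88–0.89.

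| Behaviour of the menstrual item | Power with the item |
|---|---|
| Redrawn at random each visit (50% yes), 50% menstruating | 0.79–0.80 |
| Same, 35% menstruating | 0.83 |
| Same, 20% menstruating | 0.86 |
| Fairly stable (10% of answers flip) | 0.87–0.88 |
| Responds like the other five | 0.89–0.91 |

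The first row is a loss of about 9 points. The stable case differs by about 1 point, which I treat as none. The last row is a gain of up to about 2 points.

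**Effect of adjustment.** In simulated scenarios of this kind, a model adjusted for baseline score and menstrual status had power 0.85–0.94. An unadjusted test had 0.76–0.89 on change and 0.66–0.75 on the post-treatment total. Adjustment gained power in every scenario. The scenario set is not identical to the table's, so read these as direction and rough size. Part of the gain is the general benefit of baseline adjustment and would arise without the menstrual item.

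**The case against.** The strongest reply is that this matters little. Allocation is randomised, so menstrual status is balanced in expectation, and the t test's standard error already contains the sampling variation. That stands: the error rate is nominal, and neither the PASI outcome nor the sample size uses this score.

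A reader might infer that the item can be seen only around menses, so that yes turns to no between weekly visits with the calendar. The article does not say so. It gives no recall window, and a woman may answer about her usual or most recent period. The largest power loss depends on that inference, on half of all patients menstruating in a trial open to men and to women up to 65, and on no response to treatment.

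A reader might also infer that the item should be dropped. It is one of the trial's own minor signs of BSS, and the score is built from those criteria. If the item responds to treatment, dropping it loses a little power. Removal from the main score is therefore a trade-off that the documents do not settle.

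Finally, coding conventions and covariates for a secondary score are commonly left to the case report form or the analysis plan. That is fair for the missing not-applicable code and the missing covariates taken alone. It does not cover the total itself: Table 1 states the scoring rule, and that rule puts patients on two different ranges.

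**Conclusion.** The point holds as a minor one. The six-item total has a maximum of 6 for menstruating women and 5 for all others, and the stated comparison takes no account of this. The consequence is lost precision and totals that are not comparable between patients, in one secondary outcome. There is no support for reading it as bias in the treatment comparison.

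The size cannot be fixed from the article. Under the assumptions above, the effect on power for change scores at 38 per arm runs from about −9 points to 0 to +2 points. A flat claim that the item costs 8 or 9 points of power would present a near-worst case as the expected one. The 6-against-5 range needs no assumption.

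**What to change.** State in the protocol or analysis plan that the week-4 TCM total is compared between arms by a linear model with treatment, baseline TCM score and sex as terms. Use menstrual status in place of sex if it is recorded at baseline; it is the more exact dividing line. Add the five-item total common to all patients (0–5) as a sensitivity analysis, and describe the menstrual item separately in menstruating women. Fix this before unblinding, so that the scoring is not chosen after the results are seen.

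Cost: slightly more analysis work. The baseline score and the item answers are already collected, and sex would ordinarily be among the demographic data taken at screening. Menstrual status needs at most one extra baseline question. No additional patients are needed, and the six-item score tied to the BSS criteria is kept.

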#### Safety

Safety assessments will include vital sign monitoring, routine blood tests, blood biochemistry, routine urine tests, pregnancy tests, physical examinations, and the recording of adverse events (including serious adverse events). Participants will be monitored for their vital signs, adverse events, and serious adverse events throughout the research period. Routine blood and urine tests and blood biochemistry will be conducted at the time of screening and during the 4th week of treatment. Pregnancy tests will be conducted only at the time of screening. Physical examinations will be conducted at the time of screening, during the 4th week of treatment, and throughout the follow-up period (Table 2).

**Table 2 Tab2:** Timeline for a randomized trial evaluating fire needle therapy for blood stasis syndrome of plaque psoriasis

	Research cycle	Screening period	Baseline period	Treatment period				Early termination	Follow-up period	
	Time point	Week 1	Week 0	Week 1	Week 2	Week 3	Week 4		Week 6	Week 8
**Enrollment**	**Inclusion/exclusion criteria**	**●**	**●**							
	**Informed consent**	**●**								
	**Demographic characteristics**	**●**								
	**Medical history**	**●**								
	**Registration**	**●**								
	**Randomization**		**●**							
	**Photographs of skin lesions**		**●**	**●**	**●**	**●**	**●**	**●**	**●**	**●**
**Interventions**	**Basic therapy + fire needle therapy**		**★-------------------------------------------------------------------★**							
	**Basic therapy + fire needle control therapy**		**☆-------------------------------------------------------------------☆**							
**Assessment**	**PASI**	**●**	**●**	**●**	**●**	**●**	**●**	**●**	**●**	**●**
	**BSA**	**●**	**●**	**●**	**●**	**●**	**●**	**●**	**●**	**●**
	**PGA**	**●**	**●**	**●**	**●**	**●**	**●**	**●**	**●**	**●**
	**DLQI**		**●**	**●**	**●**	**●**	**●**	**●**		
	**PRQoL**		**●**	**●**	**●**	**●**	**●**	**●**		
	**VAS**		**●**	**●**	**●**	**●**	**●**	**●**	**●**	**●**
	**TCM symptom**		**●**	**●**	**●**	**●**	**●**	**●**		
	**Recurrence rate**								**●**	**●**
**Safety**	**Vital signs**	**●**	**●**	**●**	**●**	**●**	**●**	**●**	**●**	**●**
	**Blood routine**	**●**					**●**	**●**		
	**Blood biochemistry**	**●**					**●**	**●**		
	**Urine routine**	**●**					**●**	**●**		
	**Concomitant medication**	**●**	**●**	**●**	**●**	**●**	**●**	**●**		
	**Pregnancy test**	**●**								
	**Physical examination**	**●**					**●**	**●**	**●**	**●**

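### A recurrence confirmed at Week 6 lets the patient end follow-up as well as change treatment, so Week 8 readings can be missing because the outcome was bad

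*Protocol article*

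**What the plan says.** The Primary outcomes section makes the decrease in PASI the primary outcome and says of the score: "This score will be evaluated at screening, at baseline, during the 4-week treatment period, and during the 4-week follow-up period". Table 2 places the follow-up readings at Weeks 6 and 8. BSA, PGA, VAS and adverse events are marked at the same two visits.

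Under Secondary outcomes, "recurrence is defined as a follow-up PASI score exceeding the score at the time of enrollment"; new pustules or erythroderma during follow-up also count. The row "Recurrence rate" in Table 2 is marked at Weeks 6 and 8 only. The section then states the consequence of the event: "Once recurrence is confirmed, the participant will be given the option of terminating the follow-up and initiating other treatments".

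The Statistical analysis section names ITT and per-protocol analyses. It says that non-completers were allowed for in the sample size and that their reasons and data will be recorded. Other data that are missing at random are to be counted as treatment failures. In Table 2, concomitant medication is marked from screening to Week 4 and at early termination, and is blank at Weeks 6 and 8.

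**The concern.** The option covers two separate things. Whether the patient takes another treatment is a matter for the patient and the clinician. Whether the trial goes on measuring the patient is a matter of design. Because the sentence offers both together, the event that marks a poor result also permits measurement to stop.

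On the schedule this matters at one point. Week 8 is the last visit, so a recurrence first found there costs no later data. One confirmed at Week 6 can cost all the Week 8 readings. Those patients have a PASI above the enrolment score, new pustules or erythroderma, so the Week 8 group would be selected for doing better. If the arms recur at different rates, the selection differs by arm and the Week 8 comparison of PASI, BSA, PGA and VAS is no longer the randomised one. Adverse events after Week 6 would also go unobserved in these patients.

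A second gap follows. A patient who changes treatment but does attend Week 8 has no scheduled entry there for the new treatment, so the reading could not readily be told apart from one taken without it.

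**Working it through.** **No stated figure to reproduce.** The article gives no recurrence rate. Its one related number, the 20% dropout allowance (38/0.8 = 47.5, stated as 47 per group), protects the number of patients. It does not protect the comparability of those who remain.

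**Step 1. What is recorded before a patient uses the option.** Confirmation is the condition for leaving. At Week 6 the recurrence and that visit's PASI, BSA, PGA and VAS are therefore already recorded. What can be lost is Week 8.

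**Step 2. Recurrence rate.** Let r6 be the share recurring at Week 6 and r8 the share of the rest recurring by Week 8. Counting either visit, the rate is r6 + (1 − r6) × r8. With r8 assumed at 5%:

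- r6 = 5%: 0.05 + 0.95 × 0.05 = 9.8%
- r6 = 30%: 0.30 + 0.70 × 0.05 = 33.5%

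These values are the same whether or not the Week 6 recurrers attend Week 8. The rate would fall to 5% only if it were computed from Week 8 attenders alone, and the article does not say that.

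**Step 3. Week 8 PASI in one arm.** Let r be the share who recur at Week 6 and leave, m the mean percentage reduction at Week 8 in those who stay, and k the reduction the leavers would have shown. The mean over all patients is (1 − r)m + rk. The mean over attenders is m. The overstatement is r(m − k).

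Assumptions, none of them from trial data: m = 50, k = −10 (10% worse than baseline), all Week 6 recurrers leave, and attenders only are analysed. The overstatement is then 60r:

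| r | All patients | Attenders | Overstatement (points) |
|---|---|---|---|
| 5% | 47 | 50 | 3 |
| 10% | 44 | 50 | 6 |
| 20% | 38 | 50 | 12 |
| 30% | 32 | 50 | 18 |

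**Step 4. Between arms.** With the same m and k in both arms, the error in the difference (fire needle minus control) is 60 × (r in fire needle − r in control):

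- 5% vs 10%: −3 points
- 5% vs 20%: −9 points
- 10% vs 30%: −12 points
- equal rates: 0
- 10% vs 5%: +3 points

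The sign follows whichever arm recurs more, which is unknown. The error also shrinks as k approaches m, for example if leavers improve on other treatment.

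**Step 5. Does the missing-data statement cover this?** No. An exit triggered by recurrence is not random. Counting a patient as a failure settles a yes/no outcome but gives no value for a PASI decrease.

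**The case against.** The case against is strong on several points.

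- **Recurrence rate.** A reader might infer that recurrences drop out of the rate. They do not: exit requires a confirmed event, which is therefore recorded, and nothing limits the rate to Week 8 attenders. This stands.
- **The early-termination column.** A reader might infer from the blank recurrence cell under "Early termination" that patients who flare between visits go uncounted. The assessments in that column match Week 4 row for row, including DLQI, PRQoL, TCM symptoms, laboratory tests and concomitant medication, none of which is marked at Weeks 6 or 8. It reads as an end-of-treatment visit. Recurrence is a follow-up event, so a blank cell is right there. If the visit were also used for a later exit, PASI, photographs, physical examination and adverse events would still be recorded, and recurrence could be judged from them. This stands, and no recurrence mark is needed.
- **Extent of the loss.** Leaving is optional, Week 8 is one of several PASI time points, and Weeks 1 to 4 are untouched. This stands and limits the point.
- **Analysis detail.** The attenders-only mean in the illustration is not a method the article states, and handling of values after recurrence may be set out in the full protocol or SAP, which are not shown. This stands as far as it goes: no bias in the final analysis is established. But the exit option is protocol content and is stated here, and an analysis plan can model missing Week 8 readings but cannot recover ones never taken.

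**Conclusion.** The point holds in a limited form. As written, a confirmed Week 6 recurrence permits the patient to stop being observed, so Week 8 PASI, BSA, PGA, VAS and adverse-event readings can be missing because of a bad outcome. The missing-data statement does not fit that loss. The recurrence rate is not affected, and neither are the treatment-period PASI readings or the Week 6 PASI.

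Size and direction are unknown. The 3 to 18 points within an arm, and the 3 to 12 points of between-arm difference hidden when controls recur more, rest wholly on the assumed m, k and leaving rates and on an attenders-only analysis. With other assumptions the error could be nil or reversed. This is a cheap improvement to the Week 8 data, not a threat to the trial's main comparison at the end of treatment.

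**What to change.** In the Secondary outcomes section, separate observation from treatment. Leave the option of other treatment exactly as it is, and add that a patient who takes it is asked to keep the remaining scheduled assessments: Week 8 PASI, BSA, PGA, VAS and adverse events. The patient's right to withdraw is unchanged.

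In Table 2, mark concomitant medication at Weeks 6 and 8, so that readings taken under other treatment can be flagged.

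The cost is one sentence and two marks. No visit or procedure is added. The downside is that some Week 8 readings will be made under other treatment and must be identified in the analysis, which should say how they are used.
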